#### Recruitment

As shown in Fig. 1, our pragmatic recruitment approach is conducted through a three-stage process and aims at recruiting a range of participants that would typically seek care in the primary care setting for anxiety disorders, such as new cases of anxiety disorders, longstanding sub-optimally treated patients, patients with psychiatric or physical comorbidity, patients with previous or ongoing treatment experience, etc.

**Fig. 1 Fig1:**
[figure not shown]
Flow of participants

Filter 1: We advertise the study in the general population and primary care settings through the following strategies: 1- publicity in regional newspapers; 2- targeted ads to geographic locations with Facebook and Google AdWords; 3- advertisement posters on bulletin boards of medical clinics and pharmacies, via targeted mass mail-out including a letter from the research team and a recruitment poster; 4- convenience advertisement from the research team in diverse public locations. Self-referred individuals then acquire further information on the study by consulting the study’s website or through a telephone call or email to research coordinator (AB). Self-referred individuals have to complete a brief online survey with LimeSurvey that they access through the study’s website. The screening survey contains basic eligibility criteria as well as anxiety symptoms and comorbidity overview. The survey includes the **Generalised Anxiety Disorder-7** (GAD-7) [95], a brief screening tool assessing the frequency of the 7 items in the past 2 weeks. Each item is scored from 0 (Not at all) to 3 (Nearly every day), providing a 0 to 21 severity score. To confirm that anxiety symptomatology is present, a cut point value ≥8 is used. The GAD-7 has good reliability as well as strong criterion validity. Initially designed for GAD detection, this instrument has high sensitivity and good specificity for detecting generalized anxiety disorder and other anxiety disorders [11, 96]. The survey also includes the 2-item **Patient Health Questionnaire** (PHQ-2) [97], a very brief depression screener comprising the first 2 items of the PHQ-9 [72]. The items assess the frequency of depressed mood in the past 2 weeks and are scored from 0 (Not at all) to 3 (Nearly every day), for a total severity score from 0 to 6. The instrument’s construct and criterion validity have been established. The presence of possible alcohol abuse and dependence is assessed with the **CAGE** (Cut-down, Annoyed, Guilty, Eye-opener), a widely used screening instrument [98, 99]. It comprises four items scored 0 (No) or 1 (Yes). The total score ranges from 0 to 4, with a recommended cut-off of ≥2 to screen for alcohol abuse. The CAGE has a high test-retest reliability, and adequate validity for detecting alcohol abuse and dependence in various patient populations [100]. General 1 or 2-item screening questions explore the presence of symptoms associated with Panic Disorder, Agoraphobia, Social Anxiety Disorder, Generalized Anxiety Disorder, Obsessive-Compulsive Disorder and Posttraumatic Stress Disorder in the past 6 months. Participants are asked if a health professional had already diagnosed an anxiety or mood disorders, and if they accessed resources for their anxiety in the past 2 years (support group, individual or group therapy). At the end of the survey, they provide their name and contact information. In the presence of clear exclusion criteria at the end of the survey, a list of mental health resources is provided. Filter 2: In the second stage, clinical evaluators contact individuals meeting basic eligibility criteria for a brief telephone-screening interview based on a semistructured questionnaire and clinical profile from their LimeSurvey answers. Filter 3: In the third stage, face-to-face assessment interviews are conducted with potential candidates to assess their eligibility based on the ADIS-5 assessment (T_0_).

#### Participant timeline

Data collection is managed independently of the treatment assignment by interviewers who are blind to the participant’s treatment assignment. The initial assessment (T_0_; random pre-assignment) is conducted in person and comprises completion of the consent form, the administration of the ADIS-5 and the questionnaire on sociodemographic data, health care costs, medication and work performance by a trained PhD level evaluator. Patients meeting eligibility criteria are given a participant’s booklet with the self-reported questionnaires and a stamped envelope to return the questionnaires to the research team within 48 h, and only then do we have all required information to proceed with randomization. The same booklet is being used at T_1_, T_2_, T_3_ and T_4_. The follow-up assessments take place at post-treatment (T_1;_ in person), 4 months (T_2_; service utilization only; telephone), 8 months (T_3_; in person) and 12 months (T_4_; service utilization only; telephone) follow-up.

Strategies to minimize loss to follow up include multiple study design and site personal approaches. We minimize participants’ burden and inconvenience through a minimal number of data collection, user-friendly patient booklets, secondary direct data capture through provincial administrative databases, and convenient location in a primary care or university setting. To enhance personal contact with participants, a considerate research coordinator is the primary contact throughout the trial by telephone or email. We recruited experienced interviewers and provided training for the minimization of missing data. Financial incentives ($20 CAD) are offered to participants for each in-person assessment. The group tCBT intervention is also offered to participants in the TAU group at the 12-month follow up to increase perceived health benefits associated with the trial.

### Assignment of interventions: Sequence generation, allocation concealment mechanism and implementation

Randomization is at the patient level. Contamination is unlikely because specific CBT treatments for anxiety disorders are rarely available in primary care in our health care context. To ensure that comparable groups are obtained, stratification based on site is implemented. To ensure a balance in the allocation for the strata and thus eliminate the risk of a secular trend in the composition of groups, blocks of four are used. This strategy also helps to avoid differences in the composition of the two groups, in the event of changes in clinical characteristics of those involved in the study over time. Randomization is being carried out using a code generated by a statistical software (manages the stratification and blocks) with a ratio of 1:1, set up by an independent statistician who is not be involved in the recruitment.

Allocation concealment is ensured by an online computer tool for clinical trials (PIERCE) that only releases the randomization code to the principal investigator (PR) after the baseline assessment is completed. Upon review of data entry on the PIERCE computer tool from research coordinator and clinical evaluators concerning inclusion and exclusion criteria, written informed consent, agreement to accept the randomly assigned treatment and returned participant’s questionnaire booklet, a computer command allows release of the randomization code (PR). Each member of the team (research coordinator, clinical evaluators, principal investigator) has his or her own access code to the PIERCE system, designed with several access layers, and the randomization module is only accessible to the principal investigator (PR). She informs the research coordinator of each treatment assignment based on the allocation sequence, and the treatment allocation is be communicated to participants by telephone within 2 weeks after the initial clinical interview and reception of the booklet.

#### Blinding

Blinding of trial participants and therapists is not possible in this trial. Concealment of the treatment allocation is maintained for the clinical evaluators, research team and data analyst, with the exception of the research coordinator. Participants are asked not to discuss group participation with clinical evaluators. The randomization sequence will not be broken in the data set, with random codes (“A” and “B”), until the analyses for the primary outcomes are completed. The sequence for a specific participant will be broken in case of an incident if requested by the independent Data Safety and Monitoring Committee (DSMC).

### Data collection, management, and analysis

The clinical assessment of participants is conducted in person (T_0_, T_1_, T_3_) by trained PhD level evaluators at the three sites or by telephone (T_2_ and T_4_; interview on health care costs) by the research coordinator (AB). The evaluators received a one-day training on the ADIS-5 as well as additional training to ensure optimal data collection (e.g., missing data, patient retention). Regular supervision ([name], PG) is provided to clinical evaluators throughout the duration of the data collection, particularly regarding the ADIS-5 assessments. For the post-treatment and follow-up assessments, participants also receive a letter by mail reminding them of the upcoming clinical evaluation, including a booklet with a stamped envelope. The research coordinator manages contacts with participants for scheduling assessments.

A procedure is followed to promote participant retention and complete follow-up. Treatment and follow-up are managed as different functions by different research team members, with the data collection schedule independent of treatment status and adherence to protocol. The T_2_ telephone assessment of participants contributes to avoid recall bias for service utilization as well as maintain patient’s interest in the study by regular contact with research personnel in between face-to-face assessment periods. In particular cases of participants from either groups non-compliant with follow-up assessment periods, we try to minimize the assessment burden by having them complete only the BAI primary outcome rather than the full evaluation.

Data entry, coding, storage and analysis is managed (PR) at Université de Sherbrooke on a secure server with systematic backups. Double data entry is being conducted for 10% of patient questionnaires throughout the trial to promote data quality, and data entry is under the responsibility of a trained research assistant.

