Groups are being delivered by two psychologists or psychotherapists accredited by the provincial regulatory body for the practice of psychotherapy. Primary therapists are PhD level private practice psychologists with a CBT approach and at least 2 years of clinical experience to ensure basic CBT competence for treatment fidelity. In a pragmatic perspective on treatment delivery, the co-therapists are selected by the health care managers at each study site (in-kind contribution) to reflect the range of clinical backgrounds of therapists working in the public sector in Québec. The training of co-therapists also supports capacity building and mentorship in tCBT in public sector mental health care services. Therapists’ training was initially provided during a centralized two-day workshop with the tCBT protocol developer ([name]), and followed by ongoing supervision by investigators ([name], PG). In the event of the need to recruit more therapists after the initial training session, tailored individual training are provided to therapists ([name]). Supervision ([name], PG) is provided to co-therapists at predefined times during the delivery of the intervention (pre-treatment, between sessions 3 and 4, between sessions 6 and 7, between sessions 10 and 11, post-treatment), as well as as-needed. Fidelity to the tCBT program is monitored through the recording of all treatment sessions. Therapeutic treatment adherence and competence is assessed by a random review of 30% of audio recordings during all sessions with a 5-point treatment integrity rating scale developed by the author of the intervention ([name]) [56] and used in previous trials [51, 57, 58]. Patient compliance is supported through high-quality interventions (e.g., trained and experienced therapists, supervision, monitoring treatment adherence and competence) and the provision of group interventions in a primary care setting (e.g., access, reduced mental health stigma) at convenient times (including evenings).

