
#### Questionnaires completed during therapy sessions

At the onset of each session, participants complete the **Anxiety Disorder Diagnostic Questionnaire - weekly** (ADDQ-W) [84], a version adapted from the original ADDQ [85] for session-to-session transdiagnostic assessment of change in clinical fear and anxiety. The ADDQ-W possesses strong internal consistency. After sessions 3 and 9, the participants and therapists complete the 12-item versions of the **Working Alliance Inventory (WAI)** to assess the quality of the therapeutic relationship [86, 87]. The two short-form versions of the WAI include 12 items rated on a scale ranging from 1 (Never) to 7 (Always), a greater score reflecting a better alliance. The WAI is widely used in psychotherapy, and possess established construct validity and high internal consistency [88]. After sessions 1 and 12, participants complete the 6-item **Credibility Expectancy Questionnaire** [89] which assesses their perceptions of the improvement they think and feel will occur (session 1) and that did occur (session 12). The CEQ possesses high test-retest reliability high internal consistency. After the ninth session, participants complete the **Gross Cohesion Scale** (GCS) [90], a 9-item scale evaluating the perceived cohesiveness and bond among group members. The scale has acceptable reliability and validity.

For each participant, the therapists record the following information after each session: presence, homework completion, participation level, and clinical observations. The logbook content provides a better understanding of therapists’ experience, add to the evaluation of therapeutic integrity, and contribute to the optimization of the program for future large-scale implementation of tCBT. The therapists also complete a brief questionnaire comprising sociodemographic questions, items on academic and professional backgrounds, as well as experience with CBT, group therapy and treatment of anxiety disorders.

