#### Control for bias sources

The primary means to avoid bias include the randomization scheme; the masked data collection by clinical evaluators who enrol and evaluate participants throughout the project while being uninformed of treatment assignment (with an incident report and reassignment procedure if they become unmasked); the masked research hypotheses for participants.

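### At least one investigator supervises both the tCBT co-therapists and the masked ADIS-5 evaluators, leaving an unguarded route for bias in the CSR and contradicting the blinding statement

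*Protocol article*

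**What the plan says.** Five statements in the protocol article bear on this point.

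- **Therapy supervision** (Group tCBT for anxiety disorders plus treatment-as-usual): supervision "is provided to co-therapists at predefined times during the delivery of the intervention". There are five set points per group, from pre-treatment to post-treatment, with more as needed. Two supervisors are given, one by initials.
- **Evaluator supervision** (Data collection, management, and analysis): regular supervision "is provided to clinical evaluators throughout the duration of the data collection, particularly regarding the ADIS-5 assessments". Two supervisors are again given, and the same initials appear.
- **Therapist records** (Questionnaires completed during therapy sessions): "For each participant, the therapists record the following information after each session: presence, homework completion, participation level, and clinical observations".
- **Who is masked** (Blinding): "Concealment of the treatment allocation is maintained for the clinical evaluators, research team and data analyst, with the exception of the research coordinator".
- **Masking of the raters** (Control for bias sources): the plan relies on "masked data collection by clinical evaluators who enrol and evaluate participants throughout the project while being uninformed of treatment assignment". If an evaluator becomes unmasked, an incident report and reassignment follow.

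The section on assignment of interventions adds that the principal investigator alone can release the randomization code and passes each assignment to the coordinator.

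**The concern.** The trial has two primary outcomes. The BAI is self-reported by participants who know their treatment. The CSR is a clinician's judgement on a 0 to 8 scale, and masked assessment is its main protection against expectation effects. Two secondary outcomes, high end-state functioning (CSR of 2 or lower) and responder status (CSR below 4), come from the same rating.

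A supervisor who knows that a patient is in a tCBT group, and who discusses how that patient should be scored, could influence the rating without telling the evaluator the allocation. The influence need not be deliberate. The planned inter-rater check on 25% of interviews would not reliably reveal it. The second raters are clinical evaluators too, so they come under the same supervision, and raters who share a shift still agree with each other.

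A reader of the Blinding section would also believe that nobody but the coordinator knows the allocation, which the protocol's other sections do not bear out.

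**Working it through.** **1. Is it the same person?** One set of initials stands in both supervision sentences. The other name is removed in each place, so it is unknown whether both supervisors overlap. The visible initials establish at least one shared supervisor.

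**2. Would that person know allocation?** The document does not say so directly, but it is likely. A tCBT group has 8 to 10 patients, and therapists keep notes on each one. Supervision continues through to post-treatment, close to the T1 interview. TAU participants are offered tCBT only at the 12-month follow-up, after both T1 and T3. Until then, recognising a patient as a group member reveals the arm.

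**3. Does this fit the Blinding section?** No. That section excepts only the coordinator. The principal investigator, who releases and communicates the code, is a second exception on the document's own account. An investigator who supervises the therapists is very probably a third.

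**4. Is there a stated safeguard?**

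| Safeguard in the document | Whom it covers |
|---|---|
| Evaluators uninformed of assignment | Evaluators |
| Incident report and reassignment | Evaluators who become unmasked |
| Request not to discuss group participation | Participants, towards evaluators |

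None covers the shared supervisor. The article does not say that this person is masked, sees only de-identified material, or stays out of individual T1 and T3 ratings.

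**5. Size.** No figure in the document is right or wrong on this point. The sample size serves only as a base for illustration, and it reproduces. With d = 0.45, two-sided alpha 0.03, 80% power and a two-sample t-test, n is 90.8, so 91 per arm and 182 in total; 182 / 0.85 = 214.1, so 215.

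Suppose, purely as an assumption, that a proportion p of tCBT ratings moves one CSR point in favour of tCBT and that there is no true effect. Then:

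- bias in SD units = p / SD
- z = bias × √(91/2) = bias × 6.745
- rejection rate = P(|N(z, 1)| > 2.170)

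| p | SD 1 | SD 1.5 | SD 2 |
|---|---|---|---|
| 5% | 4.0% | 3.4% | 3.2% |
| 10% | 7.0% | 4.7% | 4.0% |
| 20% | 20.6% | 10.3% | 7.0% |

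For example, with p = 20% and SD 1.5, the bias is 0.20 / 1.5 = 0.133 SD, z = 0.90, and the rejection rate is 10.3% against a nominal 3.0%. The result ranges from negligible to serious depending on p and the SD, and the document gives neither.

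**The case against.** The strongest case against is that the people who assign the CSR are stated to be masked and that a procedure exists if masking fails. The document never says that a supervisor sets, changes or approves a rating, or discloses allocation. Supervision regarding the ADIS-5 also covers the eligibility interviews before randomization, and it may concern interview technique or diagnostic criteria instead of individual post-treatment scores. Nor does the document say that patients are identified in therapy supervision. All of this stands. A reader might infer that the blinding of the CSR has been compromised, but the document does not support that.

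A reader might also see a second contradiction in the sentence "Treatment and follow-up are managed as different functions by different research team members". It belongs to a paragraph on retention and complete follow-up, and goes on to the data collection schedule. It describes how follow-up is run, and does not claim that no investigator oversees both staffs. The point should not rest on it.

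A further objection is that an article condenses the full protocol, which may describe how supervision is kept separate. That is a fair reason not to treat the missing detail as a fault in itself. It does not remove the conflict between what the article states about supervision and allocation and what it states about who is masked.

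Finally, the proportion of shifted ratings behind any error-rate figure is invented. That is correct, and the larger values in the table are not estimates for this trial.

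**Conclusion.** The point holds in a limited form. At least one investigator supervises both the therapists who deliver tCBT and the evaluators who rate the CSR. This person probably knows which patients are in tCBT, and the article states no safeguard between that knowledge and the ratings. The Blinding section's list of exceptions is incomplete: the principal investigator is missing for certain, and the therapy supervisors very probably.

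The conclusion rests on reading the shared initials as one person, and on the inference that supervision of small groups with notes on each patient makes patients identifiable. It does not show that evaluators were unmasked or that ratings moved. The size of any bias cannot be derived, and the table in the working shows only how sensitive the CSR test would be to an assumed one. The route does not affect the BAI. The point deserves action because the CSR is the only primary outcome with masked assessment and the remedy is cheap.

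**What to change.** 1. For the T1 and T3 assessments still to come, have the evaluator record and lock the CSR before any discussion with an investigator who supervises therapy. Alternatively, give ADIS-5 supervision to an existing team member with no treatment role, or to the masked evaluators among themselves.
2. Correct the Blinding section so that it lists every unmasked role, including the principal investigator and the therapy supervisors as well as the coordinator.
3. Disclose the shared supervision as a limitation for ratings already made. Enrolment ended in February 2018 and the last group was due to finish in May 2018. Many T1 ratings had therefore probably been made, while later T1 ratings and many T3 ratings were probably still to come.

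An analysis with and without the ratings discussed with a therapy supervisor is not advisable. It would select on an event after randomization, probably the harder cases, and it needs a log of discussions that the document does not mention.

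The cost is some reallocation of supervision, a procedural note and a text correction. The downside is less expert case discussion before a rating becomes final.

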#### Control for bias sources

The primary means to avoid bias include the randomization scheme; the masked data collection by clinical evaluators who enrol and evaluate participants throughout the project while being uninformed of treatment assignment (with an incident report and reassignment procedure if they become unmasked); the masked research hypotheses for participants.

